## **STATISTICAL/ANALYSIS PLAN**

### **Sample size considerations**

**Data abstracted from clinical encounter forms.** We have used ACLUSTER program to generate the number of PSC pairs (or clusters) that we will need to assess changes in contraceptive prevalence and unintended pregnancy. The first input into this program is the size of each cluster (or the number of eligible subjects available at each PSC site). There are a total of 36 FACES-supported PSC sites in Migori, Rongo, Kisumu East and Suba Districts, which are not all equal in size. The first calculation takes into account how we determine the average number of non-pregnant females of reproductive age that are potentially recruitable at each site. The other main input is the desired effect size we aim to be able to measure. Additional inputs include alpha, power and the Intra-cluster Correlation Coefficient (a measure of how similar we expect the two sites in each paired cluster to be to each other, for which we selected an intermediate value). Based on this we need 18 sites, 12 with the intervention and 6 control to be able to evaluate the integration model we propose as described in more detail below.

For the main cluster-randomized trial, the following data were inputted into the ACLUSTER program to generate an estimated number of clusters needed:

- 1. Number of subjects per cluster or site
  - a. The eligible sample includes all FACES-supported PSCs in Suba, Kisumu East, Rongo and Migori Districts. The enrollment in December 2007 at the 16 FACES-supported sites in Suba District was 10,280, at the four sites in Kisumu was 6,593, at the five sites in Rongo was 1,338, and at the 11 FACES-supported sites in Migori District is 4,882.

- b. Because there are not accurate data about the number of non-pregnant women of reproductive age at these sites, we applied estimates based on observations of client demographics at the FACES site in Kisumu, where 65% of all clients are adult females, 89% of the female population is of reproductive age, and 90% of the reproductive age females are not pregnant.
  - c. Applying these estimates, our eligible sample is approximately 12,023 women at 36 sites, an average of 333 women per site. For the sample size calculation, a conservative estimate of approximately 200 eligible women per site was used to allow for inclusion of smaller sites.
- 2. Effect size on primary outcome.
  - a. The primary outcome upon which we based our sample size calculation is contraceptive prevalence. According to the 2003 Kenya Demographic and Health Survey, approximately 22% of women in a union in Nyanza Province use a modern contraceptive method. This level of contraceptive prevalence is similar to that seen among clients at the FACES sites. We would like to be able to detect a 8% rise in contraceptive prevalence to 30%.
- 3. Assumptions
  - a. Two-sided alpha of 0.05
  - b. Power of 0.8
  - c. Intra-cluster Correlation Coefficient of 0.01
- 4. Sample size.
  - a. Using these estimates, the needed sample size is approximately 140 women at each of the 18 sites, for a total sample of 2,520 women.
  - b. We plan to initially recruit a similar number, 2,520, of male clients, however our primary outcome for men will be the proportion of male clients who report they or their partner are interested in starting a new FP method after receiving FP counseling during their visit. In order to accurately calculate this sample size, baseline data is needed to estimate the baseline proportion of male clients who would express interest in starting a new FP method. Thus, after the baseline data collection phase a more accurate sample size for male clients will be calculated.

**KAP surveys.** Because the largest sample sizes are required for expected proportions nearer to 0.5 than to 0 or 1, we will take the worst-case scenario and assume that for each individual question on the survey approximately half of the participants will answer correctly. We hypothesize that people in the intervention sites will be more knowledgeable after the intervention at the end of the study, so we would like to test for at least a ten percentage point difference in correct answers among patients in the intervention sites (~60% correct) compared to patients in the comparison sites (~50% correct), as well as a 10% increase in correct answers among patients in the intervention sites compared to the baseline results. For a one-sided test of two proportions using two samples, power of 0.8, and an alpha level of 0.05, the required sample size is 325 patients from the intervention sites and 163 patients from the comparison sites for both men (N=488) and women (N=488).

**Open-ended interviews.** A convenience sample of 30 women and 30 men will be invited to participate in the open-ended interview. The sample size for this qualitative component of the study is based on a reasonable assumption of the number of interviews needed to achieve saturation in the variety of responses obtained.

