### **Data analysis plan**

Analyses of data from the study health facilities, given the randomized cluster design, will mainly be conducted at the cluster (health facility) level. Individual level analyses will take into account

cluster effects. Primary analyses will be based on the “intention to treat” (ITT) principle, with facilities randomized to the intervention group classified as delivering “integrated services” regardless of whether or not individual women actually received integrated services.

Preliminary analyses will be conducted to compute study outcome variables and to summarize characteristics of control and treatment sites to assess the effectiveness of randomization. Initial analyses also will involve inspection of the frequency distributions of variables to identify outlying or unusual values. Following univariate descriptions of the data, bivariate and multivariate associations will be assessed as described below.

Analysis of the primary outcomes, contraceptive prevalence and unintended pregnancy rates, and the secondary outcomes, acceptability of services and knowledge related to contraception, will be based on a comparison of means or proportions between study arms using a weighted t-test that accounts for correlations between individual outcomes within sites. Even though there are only 12 health facilities in the intervention arm and 6 health facilities in the comparison arm, each mean or percentage will be based on a relatively large number of women, and the normal approximation to the binomial distribution can be used. These tests will be evaluated based on a two-sided alternative hypothesis, 80% power, and a 5% type I error rate. The same basic approach will be used for the other primary and secondary outcomes. Results will be summarized as odds ratios for models based on binary responses (e.g. use of contraception or experiencing unintended pregnancy), and mean changes for continuous responses (e.g. score on knowledge test).

As noted above, All open-ended interviews will be tape recorded (if the woman gives informed consent), transcribed, translated to English. A content analysis will be performed using the qualitative software ATLAS.ti in order to describe themes in women’s experiences undergoing contraceptive counseling, receiving family planning methods and in the acceptability of these services.

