## **EXPECTED APPLICATION OF RESULTS**

If integration of family planning services into HIV care and treatment appears feasible, acceptable, and effective at decreasing unintended pregnancies among HIV-infected women, the family planning intervention will be introduced into all FACES-supported PSC clinics. If the intervention does not appear to be feasible, acceptable, or effective based on the results of the trial, assessment of the integration will be conducted to try to identify ways in which the family planning intervention could be improved or changed. Modification of the intervention and reintroduction of it into HIV care and treatment will be considered based on trial results.

Ultimately, the findings of this research will help guide future research, policy, and interventions in the area of integrating family planning into HIV care. The ultimate goal is to create a feasible, acceptable, and effective family planning intervention that can be modified and applied elsewhere in Kenya and throughout Sub-Saharan Africa in order to increase access to effective contraception among HIV-infected women, thereby allowing them to make reproductive choices and to decrease unintended pregnancies.

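### The protocol presents the sample size and 80% power as covering unintended pregnancy, and ties rollout to that outcome, but the calculation used contraceptive prevalence only

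*Protocol*

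**What the plan says.** Four places in the protocol bear on this.

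- **Sample size considerations, opening paragraph.** The ACLUSTER program was used "to generate the number of PSC pairs (or clusters) that we will need to assess changes in contraceptive prevalence and unintended pregnancy". Both outcomes are said to be covered.
- **Sample size considerations, items 2 to 4.** "The primary outcome upon which we based our sample size calculation is contraceptive prevalence". The baseline is 22% and the target 30%, with two-sided alpha 0.05, power 0.8 and "Intra-cluster Correlation Coefficient of 0.01". The result is about 140 women at each of 18 sites (12 intervention, 6 control), 2,520 in all. No rate, effect or ICC is given for pregnancy.
- **Data analysis plan.** The sentence beginning "Analysis of the primary outcomes, contraceptive prevalence and unintended pregnancy rates" describes a weighted t-test between arms. The paragraph then says these tests are evaluated with a two-sided alternative, 80% power and a 5% type I error rate. The Endpoints section likewise lists the pregnancy rate and the percentage of pregnancies unplanned as the second primary outcome.
- **Expected Application of Results.** Rollout follows if integration appears feasible, acceptable and "effective at decreasing unintended pregnancies among HIV-infected women, the family planning intervention will be introduced into all FACES-supported PSC clinics". Contraceptive prevalence is not mentioned there.

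**The concern.** Two statements claim coverage for unintended pregnancy that the calculation does not supply, and the rollout statement then rests on that uncovered outcome. Suppose integration raises contraceptive use to exactly the 30% hoped for. The pregnancy comparison could still easily show no clear difference. A reader told that the test had 80% power would take that as evidence of no effect, and the protocol's own next step would be to reassess and modify a programme that had met the target it was sized for.

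**Working it through.** **1. Reproducing the plan's figure for contraceptive prevalence**

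Inputs from Sample size considerations: 22% versus 30%, two-sided 5%, ICC 0.01, m = 140 per site, 6 control and 12 intervention sites.

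- Design effect: 1 + (140 - 1) x 0.01 = 2.39.
- Effective controls: 6 x 140 / 2.39 = 351. The uncorrected normal formula with 2:1 allocation gives power 0.793, against 0.80 stated.
- Required size by the same formula: 358 controls x 3 x 2.39 = 2,567, against 2,520 stated (within 3%).
- Cluster-level t-test, 18 - 2 = 16 df: SE = sqrt{2.39 x [0.22 x 0.78/840 + 0.30 x 0.70/1680]} = 0.0281; noncentrality 0.08/0.0281 = 2.85; power 0.763.

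The stated size is therefore a contraceptive prevalence calculation, and the same method can be applied to pregnancy.

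**2. Assumptions for unintended pregnancy**

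The protocol gives no unintended pregnancy rate, so both inputs below are assumptions.

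- *Baseline risk 5-10%.* Sample size considerations takes 90% of reproductive-age women as not pregnant, so about 10% are pregnant. The Background gives over 50% of births unintended in Kenya (10% x 0.5 = 5%), and 97% of pregnant HIV-infected women offered treatment in rural Uganda not wanting the pregnancy (10% x 0.97 = 9.7%). The 10% is a prevalence at one time, not a nine-month risk.
- *Relative fall.* (a) If the 8-point rise acts evenly, non-users go from 78% to 70%: 1 - 70/78 = 10.3%. (b) If half of women want no pregnancy and all users are among them, non-users in that half go from 50 - 22 = 28 to 50 - 30 = 20 per 100 women: 1 - 20/28 = 28.6%. (c) A halving, for scale.

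**3. Power at ICC 0.01, 140 per site, t with 16 df**

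SE = sqrt{2.39 x [p1(1 - p1)/840 + p2(1 - p2)/1680]}; noncentrality = (p1 - p2)/SE; two-sided 5%.

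| Relative fall | Baseline 5% | Baseline 10% |
|---|---|---|
| 10.3% | 6.4% | 7.9% |
| 28.6% | 17% | 30% |
| 50% | 44% | 74% |
| Fall needed for 80% power | 74% | 53% |

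Check of the last cell: p1 = 0.10, p2 = 0.0467, SE = 0.0179, noncentrality 0.0533/0.0179 = 2.98, power 0.80.

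**4. Sensitivity**

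- The normal-approximation design-effect formula is more generous. A halving gives 56% (5% baseline) and 84% (10%), and 80% power needs falls of about 64% and 48%.
- For the 10.3% fall at 333 women per site (the protocol's average over 36 sites), power is 6.8% (ICC 0.01) to 13% (ICC 0) at 5% baseline, and 22% at 10% baseline with ICC 0.
- For the 28.6% fall at 333 per site and 10% baseline, power is 38% with ICC 0.01 and 93% with ICC 0.
- Percentage of pregnancies unplanned, taking 10% of women pregnant (6 x 140 x 0.10 = 84 versus 168 pregnancies) and 50% unplanned in controls: about 11%, 30% and 58% power for relative falls of 10%, 20% and 30% (design-effect formula).

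**The case against.** The protocol is partly open about this. It says which primary outcome drove the size, one objective in the Abstract speaks only of estimating the impact on unintended pregnancy, and the 80% sentence can be read as a general statement of test criteria. A detailed analysis plan is also promised. That softens the point but does not remove it: the opening sizing sentence names unintended pregnancy outright, the 80% sentence follows directly on that outcome, and a later analysis plan does not change either statement or the rollout wording.

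Four stronger readings are tempting and are not supported.

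- *That the trial simply has 6-13% power for unintended pregnancy.* That range depends on an assumed baseline and a fall of about 10%; other plausible inputs give clearly more.
- *That the fall cannot exceed 10.3%.* Uptake may concentrate in women who do not want pregnancy, and the protocol also expects more effective methods and better continuation. The 10.3% is one scenario, not a ceiling.
- *That three primary quantities each tested at 5% give a 14% false-positive risk.* This assumes independent tests, whereas contraceptive use and pregnancy are linked, and multiplicity is commonly left to an analysis plan.
- *That a non-significant pregnancy result triggers rejection.* The rollout text says only that integration appears effective. It sets no significance threshold, and its negative branch is assessment, modification and possible reintroduction.

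**Conclusion.** The point holds as an internal contradiction that needs no outside figure: the protocol claims sizing and 80% power for an outcome that never entered the calculation, and ties rollout to it. The size of the shortfall is conditional on the assumed 5-10% baseline and on the relative fall, but its direction is firm at the design values used for sizing (ICC 0.01, 140 women per site). Under the cluster-level t-test, power stays below 80% even for a halving of risk; under the more generous formula only a halving from a 10% baseline passes 80%. Larger sites or a near-zero ICC raise the figures, in the most favourable combinations above 80%, but the protocol's calculation rests on neither.

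**What to change.** 1. In Sample size considerations, delete the reference to unintended pregnancy from the opening sizing sentence.
2. In the Data analysis plan, limit the 80% power statement to contraceptive prevalence among women.
3. Report the pregnancy outcomes as estimates with confidence intervals and state that the trial is not powered for them. Naming contraceptive prevalence as the single primary outcome for women is the cleanest route, but optional. The alternative is to state a pregnancy rate, a target effect and the resulting power.
4. In Expected Application of Results, rest the rollout judgement on contraceptive prevalence with feasibility and acceptability, take unintended pregnancy as supportive evidence, and say that a non-significant pregnancy result will not be read as ineffectiveness.

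The cost is a protocol wording amendment and a more modest claim about pregnancy; sites, numbers and data collection do not change. If the pregnancy outcomes are moved out of the primary set, the objectives, hypothesis and endpoint sections need matching edits, and the reviewing committees would probably have to see them.

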## **1. Part I: Baseline data collection (Months 1-3)**

### **1.1. Baseline site-based data collection**

During a period of three months, baseline quantitative data on contraceptive prevalence, contraceptive methods used and pregnancy (including degree to which pregnancy was planned and desired) will be collected as part of routine clinical care at the 18 sites in Suba, Kisumu East, Rongo and Migori Districts. This information will be collected in a standardized clinical encounter form from all HIV-positive women age 18-45 at the time of each visit to the site. Data will also be collected on HIV-positive men age 18-45 regarding condom use, vasectomy and partner's use of other methods. A draft of the questions that will be used to collect the site-based data is included in Appendix A.

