### **3. Part III: Post-intervention data collection (Months 7-15)**

#### **3.1. Post-intervention site-based data collection**

Over the following nine months, data on contraceptive prevalence, contraceptive methods used and pregnancy (including degree to which pregnancy was planned and desired) will be collected, as part of routine care, at the 18 sites (twelve intervention and six control sites) among women age 18-45 and men age 18 and older. Data will also be collected on whether contraceptive counseling was performed at each clinic visit. This information will be collected in the standardized clinic encounter form from all HIV-positive women and men at the time of each visit to the site. At each of the sites, a random sample of 10-15% of all charts will be reviewed during the post-intervention period to determine if the family planning module of the clinical encounter form is being filled out. A draft of the questions that will be used to collect the site-based data is included in Appendix A.

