### **ENDPOINTS**

**Primary Outcomes** (data abstracted from clinic encounter forms from all HIV-positive clients):

1. Contraceptive prevalence
  - a. Will compare post-intervention data from intervention sites to data collected over same time period from control sites
2. Pregnancy rate (number of pregnancies/number of unique clients seen during post-intervention data collection period) and percent of pregnancies that are unplanned
  - a. Will compare post-intervention data from intervention sites to data collected over same time period from control sites

**Secondary Outcomes** (data collected from KAP surveys and in-depth interviews):

1. Knowledge of contraceptive methods among HIV-positive clients
  - a. Will compare pre-intervention rates from baseline data to post-intervention data at intervention sites

- b. Will compare pre-intervention rates from baseline data to post-intervention data at control sites
  - c. Will compare post-intervention data from intervention sites to data collected over same time period from control sites
- 2. Knowledge of contraceptive methods among providers, including peer counselors, at HIV care and treatment centers
  - a. Will compare pre-intervention rates from baseline data to post-intervention data at intervention sites
  - b. Will compare pre-intervention rates from baseline data to post-intervention data at control sites
  - c. Will compare post-intervention data from intervention sites to data collected over same time period from control sites
- 3. Acceptability of family planning services
  - a. Will compare pre-intervention rates from baseline data to post-intervention data at intervention sites
  - b. Will compare pre-intervention rates from baseline data to post-intervention data at control sites
  - c. Will compare post-intervention data from intervention sites to data collected over same time period from control sites
- 4. Feasibility of providing family planning services at HIV care and treatment centers (data from post-intervention surveys of clinic staff)
- 5. Reproductive intentions of HIV-infected clients receiving care and treatment (data from baseline client surveys and in-depth interviews)

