### **Baseline and post-intervention site-based data collection**

Informed consent will be obtained from female clients age 18-45 and male clients age 18 and above to obtain permission to abstract data from their medical records at the FACES site. They will be given information about the study and their rights as a part of the informed consent process. If they agree to allow data abstraction from their medical record, they will be asked to sign an informed consent form. As part of this informed consent process, potential participants will be informed of: (1) the purpose and methods of the study, (2) procedures to protect the confidentiality, (3) their rights to withdraw from the study at any time, (4) the fact that their participation or non-participation will not affect the medical care that they receive, and (5) persons to contact if they have any questions about the study after the completion of the interview. The participating clients will also be given a copy of the consent form to keep. This page will include names and phone numbers of persons to contact with any questions regarding the study. The consent form for clients participating in the site-based data collection is included in Appendix F. The interviewer will also ask follow-up questions to ensure that the informed consent process has been well understood by the potential participant.

**Protection against risk:** Forms for abstraction of data on the care and outcomes of HIV-positive clients will not include names or addresses, only the client's medical record number and his or her study ID number. These forms will be kept in a locked cabinet at the research office in Suba District and no one outside of the core research team members will have access to these forms.

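### The protocol does not say whether the primary analysis takes every consenting eligible woman or about 140 per site, and 140 per site gives about 73–76% power under the planned cluster-level t-test

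*Protocol*

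**What the plan says.** Three parts of the protocol bear on whose data enter the primary analysis.

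- **All clients.** ENDPOINTS describes the primary outcomes as "data abstracted from clinic encounter forms from all HIV-positive clients", and counts the pregnancy rate per unique client seen in the post-intervention period. Section 1.1 has the baseline form completed "from all HIV-positive women age 18-45 at the time of each visit to the site". Section 3.1 does the same after the intervention for women and men.
- **A numbered sample.** Sample size considerations, item 4a: "Using these estimates, the needed sample size is approximately 140 women at each of the 18 sites, for a total sample of 2,520 women". Item 4b continues in recruitment language: "We plan to initially recruit a similar number, 2,520, of male clients". Item 1c gives an average of 333 eligible women per site over the 36 candidate sites, then adds that "a conservative estimate of approximately 200 eligible women per site was used to allow for inclusion of smaller sites".
- **Consenting clients.** The informed consent section on site-based data collection makes abstraction conditional: "If they agree to allow data abstraction from their medical record, they will be asked to sign an informed consent form".

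The Data analysis plan says that facility data will mainly be analysed at cluster level, using a weighted t-test that allows for within-site correlation. It also says that a normal approximation is acceptable because each site's percentage rests on many women.

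**The concern.** These statements support two analysis sets for the same endpoint: all (consenting) eligible women seen, or about 2,520 women taken at 140 per site. At a site with more than 140 eligible women the second needs a selection rule, and there is none. The only sampling rules given are the convenience samples for surveys and interviews, and a 10–15% random chart review to check form completion.

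Two things follow. First, sites know their arm and consent is sought client by client. The Limitations section itself expects some sites to recruit more enthusiastically than others. If a number had to be filled, women could be taken in order of attendance, and attendance might differ by arm once methods are supplied on site. That is a possible risk. The protocol gives nothing from which to size it, and randomising sites does not by itself remove it. Second, the choice affects power, and the smaller set misses the stated 80% under the test the protocol names.

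**Working it through.** **Inputs, all from the protocol:** 22% against 30%; two-sided alpha 0.05; power 0.80; ICC 0.01; 12 intervention and 6 control sites; 140 women per site needed; 200 per site as the cautious planning figure; 333 per site as the 36-site average. **Assumptions:** equal site sizes, and 18 − 2 = 16 degrees of freedom for the cluster-level t-test.

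**1. Reproduce 140 per site.** Individually randomised, 2:1, pooled variance with p̄ = (0.22 + 2 × 0.30)/3 = 0.273: 358 control + 716 intervention = 1,074. Design effect at m = 140: 1 + 139 × 0.01 = 2.39. Total 1,074 × 2.39 = 2,567, or 142.6 per site, which is 1.9% above 2,520. The stated figure reproduces under a normal approximation.

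**2. Effective sizes and standard errors.** Effective control n = 6m/DE; the intervention arm has twice that. Unpooled SE = √[0.22 × 0.78/n₁ + 0.30 × 0.70/(2n₁)]; pooled SE = √[p̄(1 − p̄)(1/n₁ + 1/(2n₁))].

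| Women per site | DE | Effective n₁ | SE unpooled | SE pooled | 0.08/SE unpooled | 0.08/SE pooled |
|---|---|---|---|---|---|---|
| 140 | 2.39 | 351.5 | 0.0281 | 0.0291 | 2.852 | 2.748 |
| 200 | 2.99 | 401.3 | 0.0263 | 0.0273 | 3.047 | 2.936 |
| 333 | 4.32 | 462.5 | 0.0245 | 0.0254 | 3.271 | 3.152 |

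**3. Power.** Normal reference: critical value 1.960; the pooled version uses the pooled SE for the critical value and the unpooled SE under the alternative. t reference: noncentral t on 16 df, critical value 2.120, noncentrality 0.08/SE.

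| Women per site | Normal, pooled | Normal, unpooled | t, pooled | t, unpooled |
|---|---|---|---|---|
| 140 | 79.3% | 81.4% | 73.2% | 76.3% |
| 200 | 84.5% | 86.2% | 78.7% | 81.6% |
| 333 | 89.2% | 90.5% | 84.1% | 86.6% |

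With the t reference and unpooled variance, 80% is reached at about 177 women per site.

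**4. Which reference applies.** Many women per site make each site's percentage roughly normal. They do not add sites. When the between-site variance is estimated from 18 sites, the test statistic has about 16 degrees of freedom however many women each site contributes. The t columns are therefore the ones that match a cluster-level t-test.

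**5. Share left out if 140 is a target.** Against 200 eligible women: 1 − 140/200 = 30%. Against 333: 1 − 140/333 = 58%.

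**The case against.** The strongest reply is that a needed sample size is a requirement, not a cap. Item 4a follows the alpha, power and ICC inputs, and 2,520 is simply 140 × 18. The sections that say whose data are used name all clients, and the consent section narrows that to those who agree. The recruitment wording in item 4b concerns men, for a different outcome, and that figure is to be recalculated after baseline. Read this way, the protocol already intends what the fix asks for.

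Much of this stands: no cap is stated anywhere. But the protocol does not say that 140 is a minimum either. It calls 2,520 the total sample, although 18 sites of average size would hold 18 × 333 = 5,994 eligible women. Because each woman must be approached and must sign, field staff need to know whether to stop.

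Two further replies are fair. The shortfall to 73–76% comes from the t reference, and would exist even if 140 were clearly labelled a minimum. And the gain from analysing everyone depends on site sizes and on weights that the protocol does not name. Drawing 18 of the 36 sites at random with district-average sizes (t reference, unpooled) gives about 85% with equal or inverse-variance weights, but about 80% with weights proportional to size, against 76% at a flat 140.

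**Conclusion.** The analysis set for the primary outcome is left open between two readings and should be settled in the protocol. Under the cluster-level t-test, 140 women per site gives about 73–76% power, against 79–82% at 200 and 84–87% at 333. Keeping every consenting eligible woman therefore restores the stated 80%, or nearly so. These figures assume equal site sizes, 16 degrees of freedom and the protocol's own ICC and prevalences.

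A reader might infer three stronger things that the documents do not support:

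- **That the plan discards about 60% of eligible women.** No cap is stated. If one were meant, the share is 30–58%, and the upper end uses the average over all 36 candidate sites, not the 18 chosen.
- **That the 80% is an arithmetic error, or that power falls from a planned higher value.** The 80% was computed for 140 per site and reproduces by the normal approximation. The gap of about 10 points between 140 and 333 per site is a difference between two readings.
- **That the arms will be selected differently.** Filling a quota by order of attendance is a possibility, not something the protocol describes.

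**What to change.** Bring ENDPOINTS, Sample size considerations (item 4a) and the consent section on site-based data collection into line with one statement: the primary analysis includes every consenting eligible woman with at least one visit in the post-intervention period at each site, with no cap, and 140 per site is a planning minimum only. If a sample really is intended, state how the women are drawn at each site. Align the recruitment wording in item 4b so that it is not read as a quota.

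In item 4, restate the power at 140 per site as about 73–76% under the planned cluster-level t-test, and give the figures for 200 and 333 per site beside it.

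The wording change costs little. The real cost is more consents to obtain and more records to abstract, from a form already completed at every visit.
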